## Abstract

**Background:**

Postoperative delirium can result in increased postoperative morbidity and mortality, major demand for postoperative care and higher hospital costs. Hypnotics serve to induce and maintain anaesthesia and to abolish patients' consciousness. Their persisting clinical action can delay postoperative cognitive recovery and favour postoperative delirium. Some evidence suggests that these unwanted effects vary according to each hypnotic's specific pharmacodynamic and pharmacokinetic characteristics and its interaction with the individual patient.

We designed this study to evaluate postoperative delirium rate after general anaesthesia with various hypnotics in patients undergoing surgical procedures other than cardiac or brain surgery. We also aimed to test whether delayed postoperative cognitive recovery increases the risk of postoperative delirium.

**Methods/Design:**

After local ethics committee approval, enrolled patients will be randomly assigned to one of three treatment groups. In all patients anaesthesia will be induced with propofol and fentanyl, and maintained with the anaesthetics desflurane, or sevoflurane, or propofol and the analgesic opioid fentanyl.

The onset of postoperative delirium will be monitored with the Nursing Delirium Scale every three hours up to 72 hours post anaesthesia. Cognitive function will be evaluated with two cognitive test batteries (the Short Memory Orientation Memory Concentration Test and the Rancho Los Amigos Scale) preoperatively, at baseline, and postoperatively at 20, 40 and 60 min after extubation.

Statistical analysis will investigate differences in the hypnotics used to maintain anaesthesia and the odds ratios for postoperative delirium, the relation of early postoperative cognitive recovery and postoperative delirium rate. A subgroup analysis will be used to categorize patients according to demographic variables relevant to the risk of postoperative delirium (age, sex, body weight) and to the preoperative score index for delirium.

**Discussion:**

The results of this comparative anaesthesiological trial should whether each the three hypnotics tested is related to a significantly different postoperative delirium rate. This information could ultimately allow us to select the most appropriate hypnotic to maintain anaesthesia for specific subgroups of patients and especially for those at high risk of postoperative delirium.

**Registered at Trial.gov Number:**

ClinicalTrials.gov: NCT00507195

## Background

Postoperative delirium (PD), defined as altered perception with hallucinations, acute decline in cognition and attention and inappropriate behaviour, is a severe and relatively common clinical problem. It develops in up to 56% of the patients (higher risk in elderly patients and after orthopaedic surgery) and is related to an increase in hospital morbidity neuro-functional decline, nursing time per patient, per-day hospital costs, length of hospital stay, rates of nursing home placement and mortality rates [1,2]. Drugs used to induce and maintain anaesthesia can delay postoperative cognitive recovery and favour postoperative delirium. These unwanted effects vary according to each drug's specific pharmacodynamic and pharmacokinetic features and its interactions with the individual patients' characteristics [3,4]. The International Study of Postoperative Cognitive Dysfunction 1 (ISPOCD1), showed that general anaesthesia is related to a postoperative cognitive dysfunction at 1 week in 25.8% and 3 months postoperatively in 9.9% of the patients [5]. The ISPOCD 2 study reported, in 438 elderly patients, no significant differences in POCD between general anaesthesia and local anaesthesia at 3 months follow up (14.3% and 13.9%; p = 0.93) [6]. More recent studies suggest that POCD and PD are more common after general anaesthesia [7]. POCD at 3 months postoperatively also has major long-term consequences including a higher risk of leaving the labour market and dependency on social transfer payments, but also leads to increased mortality at a median 8.5 years [8]. None of these studies have investigated the possible effects on PD of the various anaesthetic/hypnotic regimens used to maintain anaesthesia.

This multicentre, double-blind, prospective, randomized, controlled clinical trial is designed to evaluate PD rate after general anaesthesia maintained with various hypnotics (desflurane, sevoflurane or propofol) in non-premedicated adult patients undergoing surgical procedures other than cardiac or brain surgery. We also aim to test whether delayed postoperative cognitive recovery is related to an increased risk of PD.

Postoperative Delirium and Post anaesthesia Cognitive Recovery Study: PINOCCHIO Trial

Registered at Trial.gov Number: NCT00507195, July 24, 2007

The drugs to be tested in this trial are among the most common anaesthetic hypnotics currently used for maintaining anaesthesia.

### Propofol

Propofol is an intravenous sedative-hypnotic agent used to induce and maintain anaesthesia widely used in neuroanesthesia [9-13]. Propofol infusion induces a dose-dependent vasodilation with arterial hypotension, steady-state propofol blood concentrations are generally proportional to infusion rates [3,9-11]. Propofol reduces cerebral brain flow and cerebral O_2 _metabolism to a similar extent, favourable pharmacokinetics and high-quality recovery profile despite prolonged infusion [12,13].

### Sevoflurane

Sevoflurane has several properties which make it highly useful as a day case anaesthetic. After propofol-induced anaesthesia, awakening is faster from sevoflurane than from isoflurane, faster than after propofol and comparable (in most studies) to desflurane. Subsequent recovery and discharge is generally similar after all these hypnotic agents [14-16]. Sevoflurane-induced anaesthesia is generally well-received and causes fewer side effects than propofol such as hypotension and apnea [9]. When sevoflurane is used for maintenance, the postoperative nausea and vomiting rate is comparable to that for other inhaled anaesthetics, although this complication is more frequent when used for induction. Sevoflurane's tolerability and low solubility make it easier to titrate anaesthesia and may reduce the need for opioid analgesia, thus possibly decreasing the incidence of nausea and vomiting side effects [17-19].

### Desflurane

Desflurane is a halogenated inhalational anaesthetic agent administered by vaporization and used to maintain general anaesthesia. The minimum alveolar concentration (MAC) in oxygen mixture for a 40-year-old-adult is 6% and decreases with age. Despite its high cost, together with sevoflurane, it is gradually replacing isoflurane for use in general anesthesia. It has the most rapid onset and offset of the volatile anaesthetics due to its low solubility in the blood [4,14]. The major drawbacks of desflurane are its low potency and high pungency, and that it tends to induce airway irritability and therefore, is not preferred as an induction volatile anaesthetic. On the other hand, Desflurane presents with the advantage that beyond a cut-off value of 5-6% of inspired concentration, it induces an augmented sympathetic tone with increased heart rate and arterial hypertension, instead of producing a dose-dependent peripheral vasodilatation response [19,20]. Because of the low blood-lipid coefficient that results in limited storage in theadipose tissue and the reduced risk of arterial hypotension, its use might be associated with a lower rate of postoperative delirium [4,18].

### Fentanyl

To minimize confounding variables fentanyl will be used as an opioid for pain management in all study groups. Fentanyl is an half-life opioid analgesic that interacts predominately with the μ opioid-receptor and exerts its principal pharmacologic effects on the central nervous system. Its primary actions of therapeutic value are analgesia and sedation with favorable side-effect profile. Fentanyl may increase the patient's tolerance for pain [19,20].

## Methods

The PINOCCHIO study is a multicentre, double-blind, phase II, prospective, randomized, controlled clinical trial, designed to evaluate postoperative delirium rate after general anaesthesia with various hypnotics in patients undergoing surgical procedures other than cardiac or brain surgery. A secondary end point is to detect whether delayed postoperative cognitive recovery is related to an increased risk of PD.

Enrolment criteria will be assessed in all patients during the routine preoperative assessment and physical examination. After obtaining institutional board approval (IRB), each centre will recruit and randomly assign (with a computerized randomization procedure) patients to one of three treatment arms to receive desflurane, sevoflurane or propofol for anaesthesia maintenance. Patients will be randomly assigned to one of these three strategies with equal probability. Balanced randomization will be maintained at each clinical site using a blocked randomization scheme. Patients will be randomized the day before surgery, once the patient has provided written informed consent and satisfied all the study eligibility criteria. The number of years that patients attended school will be recorded.

### Inclusion and exclusion criteria

Inclusion criteria are age > 18 and < 75 years; American Society of Anesthesiology (ASA) I-III; with no neurological deficits and Glasgow Coma Scale (GCS) Score of 15 [21,22].

Exclusion criteria: Patients with a history of drug abuse, preoperatively foreseen delayed extubation; any condition preventing proper evaluation of cognitive functions such as speech and sensory impairment or psychiatric disorders (language difficulties or psychiatric organic dysfunctions) that could make difficult to administer psychometric tests, will not be enrolled in this study.

To minimize the influence of surgical procedures on postoperative neurocognitive status, patients undergoing cardiac or brain surgery will be excluded. To reduce the risk of PD, premedication benzodiazepine or atropine will be avoided, because the use of these drugs is associated, especially in patients at higher risk, to an excess of PD incidence [23,24]. Premedication could be accomplished with fentanyl (up to 1 mcg/kg) or propofol (up to 0.5 mg/kg). All patients will receive isotonic crystalloid saline solution (5 mL/kg) before anaesthesia induction to minimize the risk of arterial hypotension after anaesthesia induction and will be preoxygenated for 3 minutes with a reservoir bag in 100% O_2 _before intubation to prevent hypoxia. After anaesthesia induction a second intravenous line will be placed for study drug administration purposes. In all patients, anaesthesia will be induced with propofol (2-3 mg/kg IV), fentanyl (2 to 4 μg/kg IV) and non-depolarizing neuromuscular blocking drugs.

After tracheal intubation, patients will be mechanically ventilated with an inspired mixture of air and oxygen (1:1). Ventilation, using a semi-closed breathing system with a fresh gas flow of at least 2 L/min during anaesthesia maintenance, will be adjusted to achieve end-tidal carbon dioxide varying from 30-35 mmHg. No local anaesthesia will be allowed. Anaesthesia will be maintained according to one of the following three study groups: *desflurane + fentanyl*: desflurane will be maintained in a 5.6 to 6.1 MAC intervals and fentanyl (2-3 μg/kg/**h **or 0.7 μg/kg boluses). If necessary, fentanyl (1-2 μg/kg/**h**) can be supplemented just before skin incision; sevoflurane + fentanyl: sevoflurane will be maintained in a 0.75 to 1.25 MAC interval and fentanyl (2-3 μg/kg/**h **or 0.7 μg/kg boluses). If necessary, fentanyl (1-2 μg/kg/**h**) can be supplemented just before skin incision; *propofol + fentanyl*: propofol will be maintained with continuous infusion at 10 mg/kg/h for the first 10 minutes, then reduced to 8 mg/kg/h for the ensuing 10 minutes and reduced to 6 mg/kg/h thereafter. If necessary, fentanyl (1-2 μg/kg/**h**) can be supplemented just before skin incision.

The administration of the assigned hypnotic (desflurane, sevoflurane or propofol) will be stopped at skin dressing. During awakening phase fresh gas flow will be increased to the "minute volume" of the individual patient. When surgery ends, residual neuromuscular blockade will be antagonized with neostigmine 2.5 mg and atropine 1 mg or glycopirrolate at 25% recovery of the first train of four (TOF)-induced twitch and patients were allowed to recover to a TOF ratio of 0.9. Administration of paracetamol (1 g IV) for postoperative analgesia, will be started at surgical wound closure and continued at the dose of 1 g 3 times/day, if necessary opioids can be used to supplement postoperative analgesia.

Postoperative (post-anesthesia) pain will be evaluated every 20 minutes, once patients reach a postoperative Aldrete score ≥ 9, for the first postoperative hour (20, 40, and 60 min) [25]. Research assistants, unaware of the group assignment, will record postoperative pain scores reported by patients during structured interviews using a verbal version of the Visual Analog Scale (VAS), in which a rating of zero corresponds to no pain, ratings of 1-4 indicate moderate pain, and ratings of 5-10 correspond to severe pain [26].

Postoperative (post-anesthesia) cognitive function will be evaluated with 2 test batteries administered individually to all patients at 4 times: before surgery (baseline), and postoperatively-after patients reach a postoperative Aldrete score ≥ 9-every 20 minutes for the first postoperative hour (20, 40, and 60 min). The Short Orientation Memory Concentration Test (SOMCT) is a patient-based test designed to assess cognitive function in terms of level of orientation, memory, and concentration. The SOMCT requires subjects to recall the current year, month, time, a complete sentence, and to repeat in numerical and reverse order the sequence of the months of the year. These 6 variables yield scores varying from 0 to 28, with higher scores indicating better cognitive function [27,28] (Appendix 1, Table 1). The Rancho Los Amigos Scale is a physician-based scale designed to quantify behavioural and cognitive status after acute brain injuries also used in the postoperative intensive care setting. Each state corresponds to 1 of 8 levels, varying from I to VIII, with higher levels indicating better behavioural and cognitive status (Appendix 2, Table 2). Both scales will be evaluated preoperatively and postoperatively by 2 experienced physicians unaware of the group assignment. If the 2 observers' score disagree, the opinion of a third observer will be considered discriminant. The Aldrete score will be assessed by a trained anaesthesiologist, blinded to the allocation treatment group [26]. Every 30-60 seconds the anaesthesiologist will score the patients' activity (ability to move extremities), respiration (ability to cough and breath), circulation (differences in blood pressure from patient's personal baseline), consciousness (ability to keep awake) and skin color (level of peripheral oxygen saturation).

The incidence of postoperative delirium will be evaluated using the Nursing Delirium Scale (Nu-Desc) a tool that can be easily integrated into routine care and clinical practice. The Nu-Desc is a five-item scale that comprises a fifth item for the rating of unusual psychomotor retardation. This scale also takes into account the subjects medical condition (delayed responsiveness, few or no spontaneous actions or words; for example, when the patient is prodded, the reaction is deferred or the patient is unarousable). A positive response to these items brings the maximal screening score to 10. A score of 2 or more on the Nu-Desc correctly identifies the presence of delirium [29,30] (Appendix 3, Table 3). The onset of postoperative delirium will be monitored with the Nu-DeSc every three hours up to 72 hours post anaesthesia.

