#### Statistical Analysis

##### Sample Size

This trial has the objective to evaluate if propofol + fentanyl, as well as sevoflurane + fentanyl, is non inferior to desflurane + fentanyl, in terms of PD. To test for non inferiority two comparisons are planned:

✓ propofol + fentanyl vs. desflurane + fentanyl

✓ sevoflurane + fentanyl vs. desflurane + fentanyl

A sample size of 275 patients for each study group, with an allocation ratio of 1:1:1, for a total of 825 patients, is required to achieve 80% power -with a significance level of 0.05- to detect a non-inferiority margin difference between the group percentage of 3% in the primary end-point variable (PD rate). The reference group percentage is 10%. The treatment group percentage is assumed to be 13% under the null hypothesis of inferiority. The power was computed for the case when the actual treatment group percentage is 7%. Sample size calculation has not been corrected for possible multiple comparisons. The statistical test used was the one-sided Score test (Farrington & Manning) [31]. Calculations were implemented in PASS2005 [32].

Patients will be randomly assigned in consecutive order in allocation blocks. No patient stratification will be done. Dunnett's test will be used after ANOVA to test the null hypothesis that no group has its mean significantly different from the mean of the reference group [33].

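### The desflurane maintenance target is printed as 5.6 to 6.1 MAC, which contradicts the article's own MAC of 6% and the sevoflurane target, and must be reconciled

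*Protocol article*

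**What the plan says.** Three statements in the protocol article bear on the desflurane target.

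- **Methods, maintenance of anaesthesia** (printed under Inclusion and exclusion criteria): "desflurane will be maintained in a 5.6 to 6.1 MAC intervals".
- **Same list, the other volatile arm:** "sevoflurane will be maintained in a 0.75 to 1.25 MAC interval".
- **Background, Desflurane:** "The minimum alveolar concentration (MAC) in oxygen mixture for a 40-year-old-adult is 6% and decreases with age". The same section describes a sympathetic response to desflurane "beyond a cut-off value of 5-6% of inspired concentration".

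The third arm has no MAC target. It is dosed by weight and time: "propofol will be maintained with continuous infusion at 10 mg/kg/h for the first 10 minutes", with two later reductions.

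The Sample Size section makes desflurane the comparator twice. The aim is to show that propofol, and separately sevoflurane, "is non inferior to desflurane + fentanyl, in terms of PD". The Results section reports that 269 patients had been enrolled by April 2011 and that two centres had local approval.

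**The concern.** MAC is a relative unit: one MAC of an agent is a particular concentration of that agent. The article puts that concentration at 6% for desflurane at age 40. A target of five to six multiples of it is therefore a very different instruction from a target near 6%. The sevoflurane arm, described in the same list and in the same unit, is centred on one MAC.

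Two things are at stake. The first is that this is an operative instruction for a randomised treatment in a recruiting trial, and it conflicts with another section of the same article. That bears on patient safety, whichever statement turns out to be the faulty one. The second is that desflurane is the reference for both planned comparisons. The trial's premise is that persisting hypnotic action favours postoperative delirium, so the amount of hypnotic specified for the reference arm is part of what the comparison means. A reader cannot tell from the article what the reference treatment is.

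**Working it through.** **Inputs, all from the protocol article**

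- Desflurane target: 5.6 to 6.1, unit printed as MAC (Methods).
- Sevoflurane target: 0.75 to 1.25 MAC (Methods).
- One MAC of desflurane: 6% at age 40, lower with age (Desflurane section). No value is given for any other age.

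**Step 1. The text as written.** Concentration = MAC multiple × 6%.

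- Lower end: 5.6 × 6% = 33.6%.
- Upper end: 6.1 × 6% = 36.6%.

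**Step 2. Against the sevoflurane arm, both in MAC.**

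- Smallest ratio: 5.6 / 1.25 = 4.48.
- Largest ratio: 6.1 / 0.75 = 8.13.
- Midpoints: 5.85 / 1.00 = 5.85.

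These ratios do not depend on the 6% figure, because both targets are printed as multiples of MAC.

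**Step 3. The same numbers read as percent.** MAC multiple = concentration / 6%.

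- Lower end: 5.6 / 6 = 0.93 MAC.
- Upper end: 6.1 / 6 = 1.02 MAC.
- Midpoint: 5.85 / 6 = 0.975, against 1.00 for sevoflurane.
- Width: (6.1 − 5.6) / 6 = 0.08 MAC, against 1.25 − 0.75 = 0.50 MAC.

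On this reading the interval lies wholly inside the sevoflurane interval at age 40.

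**Step 4. Sensitivity to the MAC value.** The article gives only 6%. The values 5% and 7% are assumptions, used to show a range.

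| One MAC | As written | Read as percent |
|---|---|---|
| 5% (assumed) | 28.0 to 30.5% | 1.12 to 1.22 MAC |
| 6% (article) | 33.6 to 36.6% | 0.93 to 1.02 MAC |
| 7% (assumed) | 39.2 to 42.7% | 0.80 to 0.87 MAC |

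Read as percent, the interval stays inside 0.75 to 1.25 MAC for any MAC value from 6.1 / 1.25 = 4.88% to 5.6 / 0.75 = 7.47%.

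**Step 5. Does the sample size depend on this?** The plan states "A sample size of 275 patients for each study group, with an allocation ratio of 1:1:1, for a total of 825 patients". With a reference rate of 10%, a true treatment rate of 7%, a margin of 3 points, one-sided alpha 0.05 and 80% power, the Farrington-Manning formula uses restricted rates of 0.0745 and 0.1045 under the null hypothesis.

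- Null variance: 0.1045 × 0.8955 + 0.0745 × 0.9255 = 0.1626.
- Alternative variance: 0.07 × 0.93 + 0.10 × 0.90 = 0.1551.
- n = (1.645 × √0.1626 + 0.842 × √0.1551)² / 0.06² = 274.85 (computed with unrounded values), rounded up to 275 per group.

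The stated figure is reproduced, and no desflurane concentration enters it.

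**The case against.** The strongest reply is that this is plainly a mislabelled unit. The numbers cluster around the 6% and the 5 to 6% quoted in the Desflurane section, and nothing signals an intention to run this arm several times deeper than the other volatile arm. The article also condenses a protocol that is not shown, so centres may be working from a correct instruction. Much of this stands: the article does not show that anyone was dosed by this sentence. But a likely slip is not a settled one. The article gives no means of choosing between a wrong unit and wrong numbers, and the conflict is in a figure it states, not in a detail left to a fuller document.

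A reader might go further and infer that the two volatile arms run at different depths on either reading, so that a delirium difference could not be attributed to the drug. The article does not support this:

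- Read as percent, the desflurane interval sits inside the sevoflurane interval with almost the same midpoint. That is a difference in permitted spread, not a systematic difference in depth.
- The fall of MAC with age, in patients over 18 and under 75, might suggest a drift between arms. The article gives no MAC at other ages and does not say whether the sevoflurane interval is age-adjusted, so no such bias can be derived.
- The propofol comparison cannot be judged on MAC at all, because propofol has no MAC target.

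**Conclusion.** The contradiction is real and should be fixed before the article is relied on as a description of the reference treatment. As printed, the desflurane target equals 33.6 to 36.6% at the article's own MAC, and 4.5 to 8.1 times the sevoflurane multiple. The percentages rest on the 6% given for age 40; the ratios rest only on the two printed intervals. Across an assumed MAC of 5 to 7%, the literal reading stays far from the sevoflurane interval.

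The finding is confined to the text. Which unit or value was meant is open, what patients received is unknown, and a difference in depth between arms is not shown. The planned 275 per group is not affected.

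**What to change.** The sponsor should reconcile the desflurane target in Methods with the MAC given in the Desflurane section. Both volatile targets should then be written in the same unit and on the same stated basis, including whether they are age-adjusted. The reconciled instruction should be confirmed with the participating centres. Which value or unit is right is for the clinical team; none is proposed here.

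Because 269 patients had already been enrolled, the sponsor should also check the existing anaesthesia records to confirm which instruction was followed.

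The cost is a protocol clarification, a notice to the centres and a review of records already held. The design, the sample size and the planned comparisons do not change.

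### The propofol + fentanyl entry states no background maintenance fentanyl, although both volatile arms have one; probably a drafting omission, but it should be corrected

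*Protocol article*

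**What the plan says.** The maintenance paragraph, printed under Inclusion and exclusion criteria, opens with "Anaesthesia will be maintained according to one of the following three study groups" and then describes each arm in turn.

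- Desflurane + fentanyl: "desflurane will be maintained in a 5.6 to 6.1 MAC intervals and fentanyl", at 2-3 μg/kg/h or in 0.7 μg/kg boluses, followed by an optional 1-2 μg/kg/h supplement before incision.
- Sevoflurane + fentanyl: "sevoflurane will be maintained in a 0.75 to 1.25 MAC interval and fentanyl", with the same background dose and the same optional supplement.
- Propofol + fentanyl: an infusion at 10, then 8, then 6 mg/kg/h, and then "and reduced to 6 mg/kg/h thereafter. If necessary, fentanyl", which begins the same optional supplement. No background fentanyl is given.

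The abstract (Methods/Design) describes all patients as "maintained with the anaesthetics desflurane, or sevoflurane, or propofol and the analgesic opioid fentanyl". The Fentanyl subsection of the Background says that fentanyl is the opioid in every group, so as to limit confounding. The Sample Size section plans two non-inferiority comparisons on the delirium rate. One of them is propofol + fentanyl against desflurane + fentanyl.

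**The concern.** The trial is meant to compare hypnotics, with the opioid held in common. An arm-by-arm dosing list is where a site would look for what to give. As printed, that list schedules a background opioid in two arms and none in the third.

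If a site followed it to the letter, the propofol and desflurane arms would differ in two respects, the hypnotic and the scheduled maintenance opioid. A difference in delirium rate, or the lack of one, could then not be attributed to the hypnotic alone. Randomisation does not help, because the arm definition itself would create the imbalance. The sevoflurane versus desflurane comparison is not affected, since those two entries carry the same fentanyl regimen.

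**Working it through.** No effect size can be computed here. The check is to set the stated opioid elements side by side. All come from Inclusion and exclusion criteria in the protocol article.

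| Opioid element | Desflurane | Sevoflurane | Propofol |
|---|---|---|---|
| Premedication fentanyl, optional, up to 1 mcg/kg | same | same | same |
| Induction fentanyl, 2-4 μg/kg | same | same | same |
| Background maintenance fentanyl | 2-3 μg/kg/h or 0.7 μg/kg boluses | 2-3 μg/kg/h or 0.7 μg/kg boluses | not stated |
| Supplement before incision, optional, 1-2 μg/kg/h | same | same | same |
| Postoperative opioids, as needed | same | same | same |

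1. *Is the dose given elsewhere?* No. The abstract, the Fentanyl subsection and the Sample Size section name fentanyl for the propofol arm, but none gives a maintenance dose.

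2. *Do the shared elements fill the gap?* Induction is common to every arm ("In all patients, anaesthesia will be induced with propofol (2-3 mg/kg IV), fentanyl"), and so is postoperative rescue ("if necessary opioids can be used to supplement postoperative analgesia"). Neither is maintenance. Beyond the optional supplement before incision, the propofol entry states no intraoperative analgesic until paracetamol at wound closure, and the same section rules out local anaesthesia. The volatile arms have a background opioid stated for the maintenance period.

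3. *Does the entry fit the rest of the article?* The abstract makes fentanyl part of maintenance in all three regimens. The arm name appears in a list of maintenance groups, so its fentanyl component refers most naturally to maintenance. The propofol entry, with only an optional supplement, fits neither.

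4. *Omission or intended difference?* The extra dose is called a supplement, which presupposes a base dose. No reason for a different opioid regimen is offered. The same paragraph has another apparent slip: desflurane is given as 5.6 to 6.1 MAC, while the Desflurane subsection puts the MAC at 6% for a 40-year-old. An omission is the likelier explanation.

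5. *Does the sample size depend on this?* No. The inputs are a reference rate of 10%, an assumed treatment rate of 7%, a 3-point margin, one-sided alpha 0.05 and 80% power. The restricted estimates under the null are 0.1045 (treatment) and 0.0745 (reference).
   - Null standard deviation term: √(0.1045 × 0.8955 + 0.0745 × 0.9255) = 0.403
   - Alternative term: √(0.07 × 0.93 + 0.10 × 0.90) = 0.394
   - n = [(1.645 × 0.403 + 0.842 × 0.394) / 0.06]² ≈ 274.9 at full precision, so 275 per group, as the article states

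   No dosing quantity enters this formula.

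**The case against.** The strongest reply is that the article already resolves the gap. The abstract, the arm name and the idea of a supplement all point to a base dose of fentanyl in the propofol arm, and a full protocol that is not shown may state it. Most of this stands, and it is why an omission is the likelier reading. It does not dispose of the point. The article did not leave the dose to another document; it printed it, with units, for two arms of three. A site or reader working from that list has to infer the third.

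Three stronger readings are tempting, and the article does not support them.

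- *That propofol patients receive no maintenance opioid.* A dose that is not stated is not a dose of zero. The article does not show how patients are actually dosed.
- *That the entry contradicts the Fentanyl subsection.* That subsection commits to the same agent in all groups, not to equal doses. Even on the literal reading the propofol arm receives fentanyl at induction. The entry fails to serve the aim of limiting confounding, but it does not break an explicit promise.
- *That delirium rates would be biased in a known direction.* One could argue that fentanyl sedates and that the Nu-DESC scores slowed responsiveness. Nothing in the article shows that such sedation lasts to an assessment or reaches the cut-off. The Discussion also cites a care package, which included treating severe pain, that lowered delirium, so less analgesia could act the other way.

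**Conclusion.** The inconsistency is real and should be corrected. Its stated size is a background of 2-3 μg/kg/h, or 0.7 μg/kg per bolus with the number of boluses not given, in each volatile arm, against no stated dose in the propofol arm. Case length and bolus frequency are also not given, so no total per case can be derived.

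The consequence is conditional. Only if sites follow the propofol entry literally does one of the two non-inferiority comparisons vary scheduled opioid together with the hypnotic. The size and direction of any resulting effect on delirium are unknown. The judgement that this is an omission rests on the wording of the article alone. The finding is about how the regimen is written; it does not show that the comparison has been compromised.

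**What to change.** In the propofol + fentanyl entry, after the infusion steps and before the optional supplement, state the same background fentanyl as in the two volatile arms: 2-3 μg/kg/h or 0.7 μg/kg boluses.

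The cost is one phrase. Sample size, power, alpha, margin, endpoint and test stay as they are. Acting promptly has some value: in April 2011 the article reported 269 of 825 patients enrolled, which leaves 825 − 269 = 556 still to be treated.
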